##### Intervention

The intervention provides structured group preparation (additional to usual care) with the aim of helping participants regain control over their drinking, prior to detoxification. Part of this control is lifestyle modification, which is necessary for maintaining abstinence post detoxification. Regaining control is linked with developing new coping skills and enhanced self-efficacy.

The six sessions are numbered and offered weekly in a given order. Stabilisation of the amount and pattern of drinking is a common theme across all the sessions. To that effect, each session can act as an entry point (i.e. an open rolling programme group), despite the special theme covered in depth during the second part. Each session has two facilitators, lasts for 1 h and is divided into three parts:In the first part (15 min), group rules are established (as advised in PPI meetings), new members are introduced, aims of the intervention, in-between sessions practice allocated in previous session reviewed as are individual targets set for the previous week are reviewed.The second part (30 min, main part) explores the following themes depending on the session number: 1—understanding habit, addiction and alcohol dependence; 2—stabilise and control your drinking; 3—lifestyle changes for you and the people around you; 4—reduction of your drinking; 5—achieving abstinence; and 6—relapse prevention strategies.In the third part (15 min), the group summarises the main learning points and agrees in-between sessions practice and targets to be achieved before the next session. A group work folder will be provided enabling notes and worksheets to be kept together, as also suggested by PPI meetings.

The number of participants per group at any point is between two and eight, as this is considered appropriate for theory-based treatment groups, to reach a balance between education, treatment, group interactions and facilitator’s attention to each participant [13]. This maximum is unlikely to be reached in the feasibility trial. If only one participant is present, the session will be offered by one of the facilitators as an individual session. The duration of 1 h as suggested in PPI, will reduce risk of withdrawal symptoms and help participants to maintain concentration.

#### Outcome measures

Feasibility outcomes will be (1) Recruitment and retention rates: we will monitor (monthly) the number of alcohol-dependent clients accessing services during the recruitment period of the study, how many meet the eligibility criteria and how many were invited and accepted into the study and retained in each group for the full 12 months. (2) Compliance with treatment: number of SPADe sessions attended (for the intervention arm) using the facilitator’s record of attendance. (3) Data collection and completeness: attendance for assessments and completeness of instruments; loss to follow-up and missing data for all outcomes will be analysed.

A variety of possible outcomes will be used, assessed at different time points (3, 6 and 12 months following randomisation), so the primary outcome for the main trial can be identified and sample size calculations conducted, including duration of continuous abstinence with no incidents of lapse or relapse; percentage of days of abstinence (PDA) (both self-report using Timeline Followback method (TLFB)) [22]; and time to relapse (from stopping alcohol to first day of alcohol use, also as defined by self-report).

Secondary outcomes will be measured using validated instruments wherever possible at the same time points as above:Severity of Alcohol Dependence Questionnaire (SADQ), a 20-item self-completion questionnaire, scores range 0 to 60 (16 to 29 indicates moderate severity, above 30 severe dependence) [23].Alcohol Urge Questionnaire (AUQ), an eight-item self-completion questionnaire containing three domains of drinking urges: desire for a drink, expectation of positive effect from drinking and inability to avoid drinking [24].Incentive conflict task (ICT). We have introduced the ICT as incentive conflict task (ICT), a newly developed task which models contributors to relapse (inherent conflict in abstaining drinkers between the intention to abstain from drinking, and the desire to drink) [9]. The ICT requires experimental subjects to abstain from responding during the presentation of a novel compound stimulus made up of two visual cues that she/he has previously learned to signal reward availability when presented separately. Thus, the task requires the subject to respond for the monetary reward, but to withhold responding under conditions in which an increased size of reward (both positive cues together) might be reasonably anticipated. In other words, ICT engages both bottom-up triggers of reward-seeking and the top-down processes that normally modulate and veto responses to such triggers. We have suggested that the task thus creates a conflict between abstaining and responding for reward similar to that experienced by the patients before relapse and that the impaired ability of multiple-detoxified patients to perform the task accurately reflects the consequences of detoxification on top-down control of their behaviour. Alcohol-dependent patients, as they experience successive detoxifications and their alcohol dependence increases, become increasingly impaired in performing the ICT [25].Euro-QoL (EQ-5D-5 L); English version [26], which is a short questionnaire assessing general healthcare used in economic evaluations for the calculation of quality-adjusted life years.Self-reported participation in aftercare activities, using a specifically developed log, measuring type and frequency of activity attended, during the period prior to the follow-up interview.

All instruments will be administered by research assistants in face-to-face assessments with participants. These assessments will take place at a convenient location for each participant, including their home. Research assistants (RA) will be fully trained to administer all outcome measures (see Table 1 below).

**Table 1 Tab1:** The use of instruments at different time points

Instruments	Baseline	3 months	6 months	12 months
TLFB (previous 90 days)	v	v	v	v
SADQ	v	v	v	v
AUQ	v	v	v	v
ICT	v	v	v	v
EQ-5D-5 L	v	v	v	v
Self-reported participation in aftercare		v	v	v

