**Methods:**

The study corresponds to phase 2 of the Medical Research Council (MRC) complex interventions guidelines which cover the development and feasibility testing of an intervention. The work is in three stages. The development, adaptation and implementation of the Structured Preparation before Alcohol Detoxification (SPADe) intervention (stage 1), a randomised feasibility study with economic evaluation (stage 2) and a qualitative study (stage 3). Fifty participants will be recruited from two community alcohol treatment services in England. Participants will be randomised in two arms: the treatment as usual arm (TAU), which includes planned medically assisted detoxification and aftercare and the intervention arm in which participants will receive structured group preparation before detoxification in addition to TAU. The main outcomes are duration of continuous abstinence with no incidents of lapse or relapse, percentage of days abstinent and time to relapse.

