#### Participants

We will recruit 50 alcohol-dependent participants, aged 18 or over who have a desire to stop drinking. As both recruiting services operate within a multi-lingual, multi-faith and multi-cultural environment, we will provide study information in the two most prevalent languages spoken by non-English speakers in our locations, in addition to the material in English. Should we recruit any non-English speaking participants to the intervention arm, the sessions will be provided in one-to one format by the intervention group facilitator, with the support of an interpreter if required. Participant flow to the study is shown in Fig. 1. We will aim to recruit at least one of the above participants in the qualitative study to explore their experience.

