#### Statistical analysis

The main analysis will be based on the intention-to-treat principle considering all randomised clients according to the arm they were allocated. As the trial is a feasibility study, the main analysis is to be descriptive and estimate the potential effect sizes and parameters required for the sample size calculation, rather than formal hypothesis testing.

The feasibility outcomes will be summarised using descriptive statistics where appropriate. The potential primary and secondary outcomes will be summarised by arm, as well as completion rates estimated for each outcome measure. Duration of continuous abstinence, as measured from randomisation, and the time to relapse, as measured from the end of the intervention, will be analysed using a Kaplan-Meier curve and log-rank test. The percentage of days of abstinence (PDA) will be analysed using a regression model. Formal hypothesis tests and confidence intervals will be conducted although due to the nature of this trial, they will be treated cautiously and the main focus will be on the completion rate of outcomes and the estimation of parameters required for a sample size calculation for the main trial.

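### Time to relapse and duration of continuous abstinence both end at the first drink and differ only in time origin, which the protocol article states inconsistently

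*Protocol article*

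**What the plan says.** The Methods part of the abstract lists three main outcomes: "The main outcomes are duration of continuous abstinence with no incidents of lapse or relapse, percentage of days abstinent and time to relapse".

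The Outcome measures section describes the first as "duration of continuous abstinence with no incidents of lapse or relapse" and gives it no starting point. It describes the third as "time to relapse (from stopping alcohol to first day of alcohol use". It gives the reason for carrying several candidates: "so the primary outcome for the main trial can be identified and sample size calculations conducted".

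The Statistical analysis section supplies the clocks: "Duration of continuous abstinence, as measured from randomisation, and the time to relapse, as measured from the end of the intervention". Both outcomes "will be analysed using a Kaplan-Meier curve and log-rank test".

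Three other statements bear on timing. Participants are randomised once they have consented (Randomisation and masking). Under usual care, detoxification is likely within 4 weeks of presentation (Trial arms, Treatment as usual). The intervention arm has six weekly group sessions before detoxification (Trial arms, Intervention).

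**The concern.** The article names lapse and relapse as two things, then defines relapse so that every lapse is one. A choice between candidate primary outcomes is informative only if the candidates measure different things. Here the two time-to-event candidates count the same event. Comparing them says nothing about whether first drink or return to sustained drinking is the better endpoint for the main trial. The intervention aims to help people regain control over drinking. If it works by stopping a lapse from becoming a relapse, neither time-to-event outcome would show that.

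The only thing that separates the two outcomes is the start of the clock, and the article gives time to relapse two different starts. Event rates and effect sizes taken from these curves are meant to feed the main trial's sample size, so the choice of clock carries forward.

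**Working it through.** The article gives no power, significance level or effect size for these outcomes, so there is no planned figure to reproduce. The check compares definitions, then illustrates how much the origin matters.

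**Step 1: the event.** Continuous abstinence ends at any lapse or relapse, that is, at any drinking. Time to relapse ends on the first day of drinking after stopping, with no amount, pattern or duration required. The terminating event is the same.

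**Step 2: the origin.**

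| Outcome | Outcome measures | Statistical analysis |
|---|---|---|
| Continuous abstinence | not stated | randomisation |
| Time to relapse | stopping alcohol | end of the intervention |

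- The two entries for time to relapse conflict. The preparation sessions come before detoxification, so their end is not the date of stopping.
- Usual-care participants receive no preparation sessions, so they have no end-of-intervention date.
- Participants are randomised before detoxification, normally while still drinking. Read literally, abstinence counted from randomisation is then zero or undefined. Read as randomisation to the first drink after stopping, it includes weeks of drinking before abstinence began.

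**Step 3: how the clocks relate.** Let *D* be the time from randomisation to stopping alcohol and *S* the time from stopping to the first drink. On the stopping clock the outcome is *S*. On the randomisation clock (second reading above) it is *D* + *S*. With a common origin the two variables and their log-rank statistics are equal. With different origins they differ by *D*, which need not have the same distribution in both arms.

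**Step 4: illustration.** From the article: 50 participants ("We will recruit 50 alcohol-dependent participants, aged 18 or over who have a desire to stop drinking"), taken as 25 per arm, and a log-rank test. Assumed, not in the article: *D* uniform on 2-6 weeks under usual care (mean 4) and 6-10 weeks in the intervention arm (mean 8); *S* exponential with the same median in both arms, so there is no true difference after stopping; complete follow-up to 52 weeks; two-sided test at |Z| > 1.96; 1500 runs per setting.

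| Median *S* (weeks) | Correlation of times | Correlation of log-rank Z | Rejected, stopping clock | Rejected, randomisation clock |
|---|---|---|---|---|
| 4 | 0.92 | 0.91 | 6.2% | 57.6% |
| 8 | 0.98 | 0.97 | 5.7% | 24.9% |
| 13 | 0.99 | 0.99 | 5.9% | 13.7% |
| 26 | 0.99 | 0.99 | 4.7% | 6.7% |

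The outcomes carry almost the same information about individuals, yet the test can reach a different conclusion. The excess rejections on the randomisation clock arise only because the intervention arm was assumed to stop 8 − 4 = 4 weeks later on average. The end-of-intervention clock was not simulated, because it cannot be formed for usual care.

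**The case against.** The strongest reply is that the outcomes, as the article plans to analyse them, are not one variable. That stands. A reader might infer that the two duplicate each other exactly, with correlation 1. The documents do not support this: the stopping-alcohol origin is attached only to time to relapse, and the only origin given for continuous abstinence is randomisation. The simulation also shows that the two clocks can lead to different conclusions.

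A reader might also infer that no event rate for relapse could ever be obtained. That is too strong. Table 1 schedules the TLFB at baseline and every follow-up, the article does not say that daily quantity goes unrecorded, and its list of outcomes is open-ended. Nor does the whole outcome set treat one drink like a full return to drinking: percentage of days abstinent and the dependence questionnaire (SADQ) both distinguish them.

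An any-drink event also suits a trial of abstinence, the main analysis is descriptive, and thresholds are often left to an analysis plan. These points limit the stakes. They do not remove the difficulty, because the article does not leave relapse undefined. It defines relapse as the first drink and states two origins for it.

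A generous reading could take the end of the intervention to mean the end of detoxification, which would fit both arms. The article, however, uses the word for the preparation sessions, which precede detoxification.

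**Conclusion.** The point holds in a limited form. Two of the three main outcomes share a terminating event, the first drink. They differ only in time origin, and the origins are stated inconsistently. They therefore do not offer two distinct candidate events for the main trial's primary outcome, and no planned time-to-event outcome separates relapse from lapse.

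This conclusion follows from the wording of Outcome measures and Statistical analysis and needs no assumption. The figures (correlations of 0.92 to 0.99; rejection in about 5-6% against 7-58% of runs) do depend on assumptions about delay and event rate. They show that the origin can matter and do not predict this trial's results. If both arms stopped drinking after similar delays, the excess rejection would not arise.

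The feasibility of the study is not in question. One of its stated purposes is weakened.

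**What to change.** 1. Keep time to first drink as the continuous-abstinence outcome.
2. Either define time to relapse separately from the TLFB daily record, or drop it as redundant. A separate definition needs a threshold fixed before any unblinded data are seen: a drinking quantity if daily quantity is recorded, otherwise a run of consecutive drinking days.
3. Reconcile Outcome measures with Statistical analysis so that each outcome has one origin that exists in both arms, and state how participants who never stop drinking are counted.

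The cost is small: revised definitions, with no new participants or instruments. The team must agree a threshold, and that choice will be partly a matter of judgement. One limit should be stated alongside it. Table 1 gives the TLFB a 90-day look-back, so the 12-month interview reaches back to about day 365 − 90 = 275. Days from about month 6 to month 9 would then lack a daily record, for first drink and relapse alike, and the derivation should say how events in that window are handled.

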### Stage 2—feasibility study

#### Design

This is a single-blind (outcome assessor blind to allocation), parallel, two-arm, feasibility RCT comparing the clinical effectiveness of SPADe as an adjunct to treatment as usual (TAU), against TAU. Participants will be assessed at baseline, 3, 6 and 12 months following randomisation. Additionally, qualitative interviews will be carried out at 3 and 9 months (see stage 3 below).

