#### Sampling

A purposive sample of participants across both trial groups and areas (approximately *n* = 20) will be interviewed at 3 months to establish experiences of randomisation, recruitment and initial trial procedures. These early interviews (wave 1) will select participants by accessing demographic details and purposefully selecting individuals across a range of variables, including age, employment status, length of time in treatment, and severity of dependence; aiming for maximum variation in the sample. Further variables may be selected for depending on the specific features of individuals recruited to the study and in consultation with the project steering group (including PPI input). Follow-up participant interviews with the same interviewees will be undertaken at 9 months (completion of the study, wave 2) to give specific feedback on retention issues and treatment conditions (specifically in relation to the control condition or receiving the intervention).

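### The 90-day TLFB look-back at the 12-month visit leaves about months 6 to 9 unobserved, so continuous abstinence to 12 months cannot be confirmed for participants still abstinent at month 6

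*Protocol article*

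**What the plan says.** The Design section fixes the schedule: "Participants will be assessed at baseline, 3, 6 and 12 months following randomisation". Table 1, under Outcome measures, labels the drinking calendar "TLFB (previous 90 days" and ticks it at all four time points, with no longer window at 12 months.

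The same section lists three candidate primary outcomes for the main trial. Two of them, "duration of continuous abstinence with no incidents of lapse or relapse; percentage of days of abstinence (PDA"), are tied to the calendar: "both self-report using Timeline Followback method (TLFB"). The third is "time to relapse (from stopping alcohol to first day of alcohol use, also as defined by self-report"), and no instrument is named for it. The Statistical analysis section says that both duration outcomes "will be analysed using a Kaplan-Meier curve and log-rank test".

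The only contact between months 6 and 12 is qualitative. The Sampling section of stage 3 says: "Follow-up participant interviews with the same interviewees will be undertaken at 9 months". It covers about 20 participants and concerns retention and experience of treatment.

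**The concern.** The interval between the last two assessments is about twice the look-back, so a block of time between them is never asked about. Continuous abstinence and time to first drink need an unbroken record up to the first drink. Once the record has a hole, the late part of both outcomes is uncertain for anyone who had not already drunk.

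Nothing else in the article fills the hole. No other Table 1 instrument is described as recording drinking by date. The service-use inventory covers contacts with services, and the 9-month interviews reach only a subsample and have another purpose.

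The estimates exist to choose the main trial's primary outcome and to size it. If the gap were ignored in the analysis, late abstinence would be overstated: a short lapse would be missed, and a relapse still going on at month 9 would be dated too late. A later analysis plan could handle the gap more carefully, but it could not recover days that nobody asked about.

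**Working it through.** The plan gives no relapse rate, event count or power figure, so there is no figure of its own to reproduce. The check is a count of calendar days, followed by an illustration under assumed hazards.

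**Coverage.** Inputs: a 90-day window (Table 1) and visits at 3, 6 and 12 months (Design). With months of 30.44 days the visits fall at about days 91, 183 and 365.

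- 3-month window: days 2 to 91
- 6-month window: days 94 to 183
- 12-month window: 365 − 89 = 276, so days 276 to 365

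Days covered: 3 × 90 = 270, and 270/365 = 74%. The gap after month 6 runs from day 184 to day 275: 275 − 183 = 92 days, and 92/365 = 25%. The other uncovered days are 1, 92 and 93, which is negligible. With 30-day months the gap is days 181 to 270, or 90 of 360 days (25%).

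**Who is affected.**

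- First drink by month 6: dated (apart from those stray days), and the participant is a known failure at 12 months.
- Dry to month 6, with a lapse that begins and ends in the gap: not seen on the TLFB.
- Dry to month 6, with a relapse that begins in the gap and continues past it: drinking is seen in months 9 to 12, but the first drink is known only to lie after month 6.
- Dry to month 6 and dry in months 9 to 12: continuous abstinence is possible but not confirmed.

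**Size (illustration).** Assume a constant hazard h of first drink per month, counted from randomisation, with S(t) = exp(−ht). The share of participants whose first drink is in the gap is S(6) − S(9). The share of all first drinks by month 12 is [S(6) − S(9)]/[1 − S(12)].

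| h per month | S(6) | S(9) | S(12) | First drink in gap | Of 50 | Share of first drinks by month 12 |
|---|---|---|---|---|---|---|
| 0.03 | 0.835 | 0.763 | 0.698 | 7.2% | 3.6 | 24% |
| 0.05 | 0.741 | 0.638 | 0.549 | 10.3% | 5.2 | 23% |
| 0.10 | 0.549 | 0.407 | 0.301 | 14.2% | 7.1 | 20% |
| 0.15 | 0.407 | 0.259 | 0.165 | 14.7% | 7.4 | 18% |

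Fixing instead the proportion who have drunk by month 12 at 50% to 90% gives a similar picture: about 11% to 15% of participants and 15% to 23% of first drinks in the gap.

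The constant hazard and the start at randomisation are simplifications. Relapse concentrated in the early months would lower these shares. Abstinence that begins some weeks after randomisation would raise them at the same hazard.

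**The case against.** The strongest reply is that much of the outcome set survives, and that several stronger readings go beyond the text.

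- A reader might infer that 12-month continuous abstinence and time to relapse cannot be measured at all. That does not follow. The first six months are almost fully covered, so early failures are dated and the 3- and 6-month versions of the outcomes stand. Only participants dry at month 6 are affected.
- A reader might take time to relapse to rest on the TLFB. The article ties the TLFB to continuous abstinence and PDA only. Time to relapse is self-reported by an unnamed route, so a dated first-drink question is not described but not excluded either.
- A reader might conclude that someone who lapsed in month 7 and then stopped will be scored as abstinent for the year. No scoring or censoring rule is given, and no 12-month horizon is stated for the Kaplan-Meier analyses. Censoring at month 6, or interval-censoring, is compatible with the text. The bias arises only if the gap is ignored.
- A reader might say that most late first drinks are lost. Among first drinks in months 6 to 12, the same hazards put 52% to 61% in the gap, from (1 − exp(−3h))/(1 − exp(−6h)). But the gap is half of that period, so at any constant hazard the share must exceed one half. Shares of all first drinks and of all participants are the fairer measures.
- The analysis is mainly descriptive and no efficacy conclusion hangs on months 6 to 9. A fixed 90-day PDA is also a sound summary, because its window is the same at every visit.

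All of this stands and limits the point. It does not remove it. The window and the schedule are stated in the article, they leave a quarter of the year unrecorded by the named instrument, and no censoring rule can detect a lapse contained within the gap.

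**Conclusion.** The point holds in a limited form. As specified, the TLFB schedule does not support continuous abstinence to 12 months for participants still dry at month 6. It does not support time to relapse beyond month 6 either, unless a separate dated question is asked. Outcomes at 3 and 6 months and first drinks before month 6 are essentially unaffected.

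The length of the gap, about 92 of 365 days, follows from the article alone. The number of participants whose first drink falls in it, about 4 to 7 of 50, rests on the assumed hazards and is an order of magnitude only. In a feasibility study that is meant to choose and size the main trial's primary outcome, this should be fixed. It does not undermine the study as a whole.

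**What to change.** In Table 1 and on the case report form, change the follow-up TLFB window from 90 days to the period since the last completed assessment. That is about 180 days at 12 months, and longer after a missed visit. Derive the first-drink date and continuous abstinence from the full calendar. Keep last-90-day PDA as a derived summary so that the visits remain comparable.

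No new visit or staff is needed. The price is a longer 12-month interview and more recall error for months 6 to 9; the documents give no basis for saying how much more.

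If the window stays as it is, either limit the continuous-abstinence and time-to-relapse analyses to 6 months, or treat times after month 6 as censored or interval-censored. In the second case, state that lapses lying wholly within the gap cannot be detected.
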